|----------------------------------------------------------------------------------------------------------------------------|-------------------------------------------------------------------------------------------------------------------------------------------------------------------------------------------------------------|------------------------------------------------|
|                                                                                                                            | Overall survival                                                                                                                                                                                            | Up to and including day 60                     |
|                                                                                                                            | Inpatients only:
Viral clearance on or before d8 **                                                                                                                                               | Day 8                                          |
|                                                                                                                            | Inpatients only:
Duration of pyrexia in days (defined as a temperature $\geq 38^{\circ}\text{C}$ )                                                                                                | Up to and including day 60                     |
| Evaluate the safety and tolerability of favipiravir in the study population                                                | Adverse events                                                                                                                                                                                              | Up to and including day 60                     |
| Exploratory objectives                                                                                              | Exploratory endpoints                                                                                                                                                                                | Timepoint of assessment                 |

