| Pregnancy Test                                                      | X                              |                 |          |                 |          |          |          |          |                 |          |           |                        |                                    |                                     |
| PK testing                                                          |                                | X               |          | X               |          | X        |          |          | X               |          | X         |                        |                                    |                                     |
| COVID19 Health
and Wellbeing
Follow up
Survey
(Appendix 3)          |                                |                 |          |                 |          |          |          |          |                 |          |           | X                      | X                                  | X                                   |

1. Observations: Heart rate, temperature, oxygen saturations, blood pressure, respiratory rate
2. IMP should start to be administered within 24 hours of randomisation
3. Bloods/Nasopharyngeal swabs can be taken +/- 48 hours from scheduled time point unless otherwise specified. Screening bloods/NP swabs should be performed within 96 hours of randomisation
4. Nasopharyngeal swabs on day 1 should be taken as close to T0 (time of first drug administration) as possible
5. Patients discharged prior to day 15 should follow the outpatient schedule of assessments from point of discharge. Patients should return for clinic visit where possible, or be followed up by phone call if unable to attend

6. Follow-up visit at day 29 and 60 may be performed by telephone if patient is unable to attend clinic
7. Serum pregnancy test, for patients of child bearing potential only
8. Screening COVID-19 test can be done using any valid method of testing
9. PK Samples should be taken at the following times:

- Day 1: pre dose and 0.5 hours post dose
- Day 3: pre and 0.5 hours post dose
- Day 5: pre and 0.5 hours post dose
- Day 8: Pre dose
- Day 10: Pre dose

In addition, 16 volunteers (8 male, 8 female) will have more frequent sampling for PK on days 1 and 3 after either dose that day. Hours post dose: 0.5, 1, 2, 7, 12

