### **Schedule of Events for outpatients**

| Investigation                                | Screening
(d-4 to
d1) | Day
1                                             | Day
2 | Day
3 | Day
4 | Day
5 | Day 6 | Day 7 | Day 8 | Day 9 | Day 10 | Day 15                                      | Follow-up(day
29)  | Follow-up(day
60)  |
|----------------------------------------------|-----------------------------|------------------------------------------------------|----------|----------|----------|----------|-------|-------|-------|-------|--------|---------------------------------------------|-----------------------------------|-----------------------------------|
| Written
informed
consent               | X                           |                                                      |          |          |          |          |       |       |       |       |        |                                             |                                   |                                   |
| Demographic
and Medical
History        | X                           |                                                      |          |          |          |          |       |       |       |       |        |                                             |                                   |                                   |
| Randomisatio
n                            | X                           |                                                      |          |          |          |          |       |       |       |       |        |                                             |                                   |                                   |
| Observations                     | X                           |                                                      |          |          |          |          |       |       |       |       |        | X                                           | X                                 | X                                 |
| Height and
weight                         | X                           |                                                      |          |          |          |          |       |       |       |       |        | X                                           | X                                 | X                                 |

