| COVID19 Health
and Wellbeing
Follow up
Survey
(Appendix 3)          |                             |                 |          |          |          |          |       |       |                |       |        | X      | X                                 | X                                 |

1. Observations: Heart rate, temperature, oxygen saturations, blood pressure, respiratory rate
2. IMP should start to be administered within 24 hours of randomisation

3. Bloods/Nasopharyngeal swabs can be taken +/- 48 hours from scheduled time point unless otherwise specified. Screening bloods should be performed within 96 hours of randomisation
4. Nasopharyngeal swabs on day 1 should be taken as close to T0 (time of first drug administration) as possible
5. Follow-up visit at day 15, 29 and may be performed by telephone if patient is unable to attend clinic
6. Serum pregnancy test, for patients of childbearing potential only. Result must be confirmed negative before IMP is released to patient.
7. Screening COVID-19 test can be done using any valid method of testing
8. AE, con med and WHO COVID Ordinal Severity Scale assessments should be made by phone call on days 1 – 10.
9. Optional nasopharyngeal swab may be done by patient at home if possible and safe to transport
10. To minimise the time spent in the clinic, patients can return home after screening and have IMP delivered to their home following randomisation
11. PK sampling should only be done where site have provision to take a predose sample (screening or day 1 pre-dose) AND a post dose sample (30 minutes after dosing), and have facilities to spin samples within 4 hours.

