### **Day 1-10^1**

WHO COVID 10 point ordinal severity scale assessment (daily – worst value in last 24 hours)

Documentation of concomitant medications (daily)

Assessment of adverse events (daily)

Routine observations/vital signs\* (daily)

Routine clinical blood tests: days 1,3,8,11 (+/- 48 hours)

Blood tests for immunological and epigenetic testing: days 1, 3 (+/- 48 hours)

Symptom directed clinical examination if clinically indicated

Administration of IMP (if applicable)

Nasopharyngeal swab (for SARS-CoV-2 PCR assessment and Viral Load): days 1 (at time of first dose), 3, 8, 10, 13 (+/- 48 hours)

Pharmacokinetic samples: according to the sample schedule (Appendix 5)

 Patients discharged during this time should follow the outpatient trial schedule. The timing of the first dose of favipiravir should be documented as Time zero (T0). The nasopharyngeal swab should be taken as close to this time as possible.

 On day 8, two swabs should be taken – one to be sent for immediate COVID-19 testing by any valid method, the other to be stored for later analysis of viral load.

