### **Day 1-10^1**

Dispensing of IMP (patients on favipiravir arm)  
WHO COVID 10 point ordinal severity scale assessment (daily – worst value in last 24 hours)  
Documentation of concomitant medications (daily)  
Assessment of adverse events (daily)  
Nasopharyngeal swab (for SARS-CoV-2 PCR assessment and viral load): day 8  
Administration of IMP and completion of Patient Diary (patients on favipiravir arm)

 Assessments on day 1-10 will be performed by telephone

 IMP may be dispensed in clinic following randomisation where possible, or couriered to the patient's home

 NP swab may be performed at home by the patient provided this is safe to do and safe transport to research laboratory has been arranged.

 Baseline PK sample can be taken at screening or pre-dose day 1. PK sampling will only be undertaken where sites can accommodate both pre and post dose sampling, and have the facilities to spin samples within 4 hours.

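### The end of fever cannot be dated for inpatients who go home febrile or whose fever returns at home, because no temperature is scheduled between discharge and day 15

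*Protocol*

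**What the plan says.** Protocol Table 1 lists, for inpatients only, "Duration of pyrexia in days (defined as a temperature" of 38°C or above, assessed up to day 60. Section 7.1.3 analyses it by Fine and Gray regression from the onset of pyrexia, or from admission if the patient is already febrile at randomisation. Death before resolution is the only competing event named. The section does not define the day on which pyrexia ends, and it does not mention discharge.

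In hospital, section 4.2.1 requires "Routine observations/vital signs" daily on days 1 to 10. The inpatient table also marks days 15, 29 and 60.

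At discharge the schedule changes. Footnote 5 of the inpatient table reads: "Patients discharged prior to day 15 should follow the outpatient schedule of assessments from point of discharge". Section 4.2.1 repeats it for days 1 to 10: "Patients discharged during this time should follow the outpatient trial schedule".

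In the outpatient table, temperature sits in one row, defined in footnote 1 as "Observations: Heart rate, temperature, oxygen saturations, blood pressure, respiratory rate". That row is marked at screening and on days 15, 29 and 60, and is blank on days 1 to 10. Section 4.2.2 says "Assessments on day 1-10 will be performed by telephone", and footnote 8 sets their content: "AE, con med and WHO COVID Ordinal Severity Scale assessments should be made by phone call on days 1" to 10. Temperature is not on that list. The home diary in section 5.5 records doses.

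**The concern.** Time to the end of fever needs serial temperatures up to that end. The protocol promises follow-up to day 60, but its schedule stops serial measurement when the patient leaves the ward. A patient who goes home at 38.5°C has a known start of fever and no datable end.

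Discharge happens after randomisation and is decided open label, and the protocol treats length of stay as an outcome that favipiravir may change (exploratory endpoint, Table 1). If the arms differ in when patients go home, they differ in how much fever goes unobserved. The treatment comparison then depends partly on how the analyst handles discharge. An analysis plan can fix that rule, but it cannot recover readings that were never collected.

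**Working it through.** The protocol states no figure to reproduce. The check has three parts.

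**1. Days without a scheduled temperature before day 15.** For discharge on day d, with d no later than 10, the last ward reading is on day d and the next scheduled reading is on day 15. The gap is 14 − d days. A patient who stays in hospital has no scheduled trial reading on days 11 to 14, which is 4 days. The part due to the change of schedule is therefore (14 − d) − 4 = 10 − d.

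| Discharged on day | Days without a scheduled reading | Of these, due to the switch |
|---|---|---|
| 2 | 12 | 8 |
| 3 | 11 | 7 |
| 4 | 10 | 6 |
| 5 | 9 | 5 |
| 7 | 7 | 3 |
| 10 | 4 | 0 |
| still in hospital | 4 | – |

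The day 15 reading is itself uncertain. Both tables mark it, but the day 15 lists in sections 4.2.1 and 4.2.2 do not name observations, and both sections allow a telephone contact instead of a visit.

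**2. Could discharge differ by arm?** The day 15 control assumptions in section 7.1 put 2 + 16 + 16 = 34% of patients in the ambulatory categories. The favipiravir column at the target odds ratio puts 2.3 + 21.8 + 27.0 = 51.1% there, about half. These figures include patients who entered as outpatients and say nothing about fever. They do show that the design expects fewer patients in hospital on favipiravir.

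**3. Direction of bias by handling rule.** All inputs here are assumptions, not protocol figures: no true effect on fever, mean fever 4 days, mean time to discharge 6 or 12 days on control, and a discharge rate ratio h of 1.0, 1.3 or 1.6 for favipiravir. Fever and discharge are either independent or share a gamma frailty of variance 1. There are 200,000 simulated patients per arm, and the ratio is events per person-time to day 15. It is not a Fine and Gray fit, and deaths are not modelled.

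| Rule for patients febrile at discharge | Apparent ratio, h = 1.3 to 1.6 | h = 1.0 |
|---|---|---|
| Discharge counts as resolution | 1.05 to 1.23 | about 1.00 |
| Resolution dated at day 15 | 0.86 to 0.97 | about 1.00 |
| Censored at discharge | 0.93 to 1.00 | about 1.00 |

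The true ratio is 1.0, and a value above 1 favours favipiravir. Censoring at discharge is clearly biased only when fever and discharge are correlated.

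The first row can be checked by hand for the independent case. The share of control patients febrile at discharge is p = (1/m) ÷ (1/m + 1/4) = 4/(4 + m), where m is the mean time to discharge. This is 0.40 for m = 6 and 0.25 for m = 12. The apparent ratio is (1/4 + h/m) ÷ (1/4 + 1/m) = 1 + p(h − 1). For p = 0.40 and h = 1.6 this is 1.24 (simulated 1.233). For p = 0.25 and h = 1.3 it is 1.075 (simulated 1.075).

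The formula shows how the bias depends on p. If only 5% were febrile at discharge, the ratio would be 1 + 0.05 × 0.3 = 1.015 to 1 + 0.05 × 0.6 = 1.03. The simulated scenarios have 25% to 40% febrile at discharge on control and, for h = 1.3 to 1.6, 30% to 52% on favipiravir.

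**The case against.** The strongest reply is that the gap touches only some patients. If fever ends on the ward within days 1 to 10, daily observations date it. A patient sent home sooner because fever settled sooner has an observed end. The documents do not say how many inpatients leave febrile. Early discharge cannot simply be assumed either: entry is at WHO level 2 to 4, but a predicted in-hospital mortality of at least 10% is also required, and the control assumptions have 5 + 7 + 5 + 13 + 13 + 12 = 55% in hospital at day 15. All of this stands and limits the point to patients febrile at discharge or with recurrence.

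A reader might infer that the gap hides or reverses a real benefit. The documents do not support a direction: section 7.1.3 gives no rule for discharge, and the sign changes with the rule. A reader might also infer that durations are overstated by a fixed amount. Going home febrile on day 4 with true resolution on day 6 would give 15 − 6 = 9 days too many, but only if resolution is dated at the day 15 reading, which the protocol does not say.

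Two sources soften the gap. Adverse events carry start and stop dates (section 6.1.2.2), so the daily calls could pick up some returning fever. They would supply no reading against 38°C, and fever continuing from entry may not be recorded as an event. For patients still in hospital on days 11 to 14, what is missing is a scheduled trial entry. Section 4.2.1 marks daily observations on days 1 to 10 as standard care, so chart readings probably exist afterwards too.

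Handling of discharge may also be set in an analysis plan that is not shown. That answers the question of the rule, but it does not supply the missing temperatures.

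**Conclusion.** The point holds in a limited form. For inpatients still febrile at discharge, or whose fever returns at home, the schedule collects no temperature from which the end of pyrexia can be dated before day 15, and perhaps none then. For discharge on days 2 to 10 the gap is 12 down to 4 days.

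The treatment comparison on this endpoint can be biased if discharge differs by arm. Under the assumed inputs the apparent ratio, with no true effect, runs from about 0.86 to 1.23 depending on the handling rule. It moves towards 1 as the share febrile at discharge falls, and it is about 1 if favipiravir does not change discharge. The documents give neither the share nor the rule, so neither the size nor the direction can be stated for this trial.

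Severity is minor. One secondary endpoint, in inpatients only, is affected. The primary endpoint, sample size and alpha are not.

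**What to change.** - Add one item to the day 1 to 10 calls, in footnote 8 of the outpatient table and in section 4.2.2: has the temperature been 38°C or above since the last call (yes/no, with the highest reading if one was taken).
- At day 15, by visit or telephone, ask for the date of last fever. This also covers days 11 to 14 for patients at home, when no calls are scheduled.
- For patients still in hospital on days 11 to 14, take the temperature from the routine chart.
- In section 7.1.3, define the end of pyrexia as the last day with a recorded or reported temperature of 38°C or above, with the same rule in both arms.

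The cost is one field on calls already made in both arms, one question at day 15, and chart transcription for patients still in hospital. The downside is that home readings are less precise than ward readings and are self-reported in an open-label trial, so reporting could itself differ by arm.

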**PK samples require to be spun within 4 hours of being taken – where sites do not have the facility to do this, PK's will be omitted.**

10. Blood samples for epigenetic and immunological testing should be taken at the time of the first PK draws on days 1 and 3 (i.e. pre-dose)
11. Two NP swabs should be taken on day 8 – one for immediate COVID-19 testing (any valid method) and one to be stored for later viral load analysis.

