| Explore the immunological and biometric markers contributing to the clinical condition of patients in the study population | Evaluate the relationship between immunological and biometric markers and the clinical outcomes of the study                 | Up to and including day 60              |
| Post COVID19 health and psycho-social consequences                                                                         | Evaluate the relationship between post COVID-19 health and psycho-social consequences and the clinical outcomes of the study | Up to and including day 60              |

\*See Appendix 1 for WHO COVID-19 10 point ordinal severity scale.

\*\* Defined as a negative SARS-CoV-2 PCR result

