#### 4.3.2 Valid COVID19 Test for diagnosis and viral clearance

An appropriate sample (usually a nasopharyngeal swab) will be collected and sent to local NHS laboratories for processing for diagnosis. Viral clearance on day 8 for inpatients will also be processed at a local NHS laboratory. Viral clearance at day 8 for outpatients will be collected at home by patients and sent to local academic laboratories for processing, provided it is feasible and safe to do so.

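### Day-8 viral clearance is defined by PCR, but the clearance swab may be read by any valid method and is called optional after discharge, so the endpoint is open to misclassification and recovery-related missingness

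*Protocol*

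**What the plan says.** Table 1 (Trial Summary and section 2) lists viral clearance on or before day 8, inpatients only, as a secondary endpoint. Its footnote gives the definition: "Defined as a negative SARS-CoV-2 PCR result". The same measure in outpatients is exploratory.

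On how the inpatient day-8 sample is tested:

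- Schedule of Events for inpatients, footnote 11, describes two swabs: "one for immediate COVID-19 testing (any valid method) and one to be stored for later viral load analysis".
- Section 4.2.1, Day 1-10, footnote 2, gives the same instruction: "one to be sent for immediate COVID-19 testing by any valid method, the other to be stored for later analysis of viral load".
- Section 4.3.2, whose heading covers valid tests for both diagnosis and clearance, says: "Viral clearance on day 8 for inpatients will also be processed at a local NHS laboratory". It names no assay.

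On discharge, footnote 5 of the inpatient schedule says: "Patients discharged prior to day 15 should follow the outpatient schedule of assessments from point of discharge". Section 4.2.1, Day 1-10, footnote 1, says the same for discharge during days 1 to 10. On the outpatient schedule, footnote 9 describes the day-8 sample as: "Optional nasopharyngeal swab may be done by patient at home if possible and safe to transport". Section 4.2.2, Day 1-10, lists that swab without calling it optional; its footnote lets the patient take it at home if that is safe and transport is arranged. Section 4.3.2 says outpatient samples are "sent to local academic laboratories for processing, provided it is feasible and safe to do so".

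**The concern.** There are two separate weaknesses.

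**Assay.** The definition requires PCR; the collection instructions do not. A site that follows footnote 11 to the letter can return a day-8 result that does not meet the definition. If a negative on a less sensitive test is then counted, some patients who are still PCR-positive are recorded as cleared. When this happens equally in both arms, it pulls the treatment difference towards zero.

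**Collection.** Discharge happens after randomisation, generally reflects improvement, and is decided in an open-label trial. If discharged inpatients are less likely to give a day-8 swab, missing results are tied to recovery. The protocol also does not say whether such a patient stays in the inpatient secondary endpoint or moves to the exploratory outpatient one.

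This is the only virological secondary endpoint; change in viral load is exploratory. Faster viral clearance is part of the protocol's stated case for the drug (Background and section 1.1), so the endpoint should measure what its definition says.

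**Working it through.** The protocol gives no clearance rate, effect size or power for this endpoint, so there is no figure to reproduce. The contradiction rests on the text. The arithmetic only shows possible size, on assumed rates.

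**1. Text comparison**

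| Place | Assay for day-8 clearance |
|---|---|
| Table 1 footnote | PCR |
| Inpatient schedule, row heading | PCR |
| Section 4.2.1, swab line | PCR assessment and viral load |
| Inpatient schedule, footnote 11 | any valid method |
| Section 4.2.1, footnote 2 | any valid method |
| Section 4.3.2 | local NHS laboratory, assay not named |

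The two footnotes qualify the very entries that name PCR, so the text conflicts within the schedule and within section 4.2.1. The second swab is kept for viral load, and no section assigns it to clearance.

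**2. Misclassification**

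Assumptions: p is the true PCR-negative rate. The alternative test detects a fraction s of PCR-positives and never reports a positive where PCR is negative. A share w of patients is tested this way, with s and w equal in both arms.

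Let f = w(1 − s). Observed negative rate = p + (1 − p)f, and observed difference = (1 − f) × true difference.

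With true rates of 40% and 60%, OR = (0.60/0.40)/(0.40/0.60) = 2.25.

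| w | s | Control | Experimental | Difference (points) | OR |
|---|---|---|---|---|---|
| 1 | 0.8 | 0.40 + 0.60×0.20 = 0.52 | 0.60 + 0.40×0.20 = 0.68 | 16 | (0.68/0.32)/(0.52/0.48) = 1.96 |
| 1 | 0.7 | 0.40 + 0.60×0.30 = 0.58 | 0.60 + 0.40×0.30 = 0.72 | 14 | (0.72/0.28)/(0.58/0.42) = 1.86 |
| 0.5 | 0.8 | 0.40 + 0.60×0.10 = 0.46 | 0.60 + 0.40×0.10 = 0.64 | 18 | (0.64/0.36)/(0.46/0.54) = 2.09 |
| 0.5 | 0.7 | 0.40 + 0.60×0.15 = 0.49 | 0.60 + 0.40×0.15 = 0.66 | 17 | (0.66/0.34)/(0.49/0.51) = 2.02 |

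Other assumed rates give a similar picture. With 30% and 50% (OR 2.33) and w = 1, s = 0.8 gives 44% and 60% (OR 1.91), and s = 0.7 gives 51% and 65% (OR 1.78). If PCR is used throughout (w = 0), there is no loss.

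**3. Missing swabs after discharge**

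Assumptions: clearance is 60% in patients discharged by day 8 and 30% in those still in hospital, in both arms. The share discharged, d, is 30% in control and 50% in experimental. A fraction m of discharged patients gives a swab, regardless of clearance.

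True rates: 0.3×0.6 + 0.7×0.3 = 39%, and 0.5×0.6 + 0.5×0.3 = 45%, a difference of 6.0 points.

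Observed rate = (d·m·0.6 + (1 − d)·0.3)/(d·m + 1 − d).

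- m = 0.5: control 0.30/0.85 = 35.3%, experimental 0.30/0.75 = 40.0%, difference 4.7 points.
- m = 0.25: control 0.255/0.775 = 32.9%, experimental 0.225/0.625 = 36.0%, difference 3.1 points.

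These figures assume that no other swab supplies the result.

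**The case against.** The best defence of the assay wording is that the definition is the only scoring rule in the protocol. It says PCR, the schedule row is headed PCR, and the section 4.2.1 swab line mentions PCR assessment. No sentence says that a negative by another method counts, and PCR is itself a valid method. This stands against any claim that results will be misclassified. It does not remove the conflict, because section 4.3.2 takes the inpatient clearance result from the local test without requiring PCR, and nothing directs anyone to the stored swab when that test was something else.

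On missing swabs, the defence is stronger. The endpoint is clearance on or before day 8, inpatients also have a PCR swab on day 3, and swabs may be taken within 48 hours either side of the scheduled time. A day-8 swab can therefore be taken on day 6 or 7, before discharge. The outpatient schedule still lists a day-8 swab, and only footnote 9 makes it optional. A result is lacking only when a patient leaves before the window opens, has no earlier negative, and gives no later swab. This narrows the loss but does not close the gap.

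The numbers rest on rates that are not in the protocol, and the largest effects assume that every patient is tested by a non-PCR method. The stored swab could also supply PCR results for patients still in hospital, since section 4.3.3 refers to viral PCR testing of viral-load swabs; but no section provides for that use.

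**Conclusion.** The concern holds in a limited form. The PCR definition and the any-valid-method instructions conflict and must be reconciled. As written, the endpoint is open to misclassification that would dilute the arm difference. Under the assumed 40% and 60%, the OR falls from 2.25 to 1.96 or 1.86 if every patient is tested at relative sensitivity 0.8 or 0.7, and to 2.09 or 2.02 if half are. Missing results related to recovery are possible because footnote 9 of the outpatient schedule and section 4.2.2 differ on whether the swab is optional.

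A reader might infer that the endpoint is in fact misclassified and selectively missing, or that early recoverers as a group will have no result. The document does not support that: it gives no frequency for non-PCR testing, for discharge before the window or for missed swabs. How deaths before day 8 and absent swabs are scored can be left to the SAP, which is not shown, and is not part of this point.

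The effect is confined to a secondary endpoint. The day-15 primary endpoint, the 302-patient sample size and the interim boundaries do not depend on it.

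**What to change.** 1. State in the inpatient schedule (footnote 11), section 4.2.1 (Day 1-10, footnote 2) and section 4.3.2 that day-8 clearance is scored from PCR only. Where the immediate test was not PCR, score it from PCR on the second, stored day-8 swab. Sites may still run the immediate test by another method.
2. Reconcile footnote 9 of the outpatient schedule with section 4.2.2. State that patients who were inpatients at randomisation remain in the inpatient endpoint after discharge and are scheduled for the day-8 swab by the existing home or clinic route, keeping the stated feasibility and safety condition.

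The cost is a wording amendment, PCR on swabs already planned for collection and storage, and some courier and laboratory work for discharged patients. This should be small, although the protocol gives no costs. Some swabs will still be missed where home collection or transport is not safe.
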